# Comparative effectiveness of low-level laser therapy versus muscle energy technique among diabetic patients with frozen shoulder: a study protocol for a parallel group randomised controlled trial

**DOI:** 10.1186/s13018-024-04735-7

**Published:** 2024-04-30

**Keywords:** Conventional therapeutic exercises, Diabetes mellitus, Frozen shoulder, Low-level laser therapy, Muscle energy technique

## Abstract

**Background:**

Diabetes mellitus is one of the fastest-growing health challenges of the twenty-first century with multifactorial impact including high rates of morbidity and mortality as well as increased healthcare costs. It is associated with musculoskeletal complications, with frozen shoulder being commonly reported. While low-level laser therapy (LLLT) and muscle energy technique (MET) are commonly used to manage  this condition, there remains a lack of agreement on the most effective approach, with limited research available on their comparative efficacy.

**Objectives:**

To evaluate the comparative effectiveness of LLLT versus MET among diabetic patients with frozen shoulder.

**Methods:**

This is a single-centre, prospective, single-blind, randomised controlled trial with three parallel groups to be conducted at Ahmadu Bello University Teaching Hospital, Zaria, Kaduna State, Nigeria. Sixty diabetic patients with frozen shoulder will be randomly assigned into LLLT group, MET group, or control group in a 1:1:1 ratio. All the groups will receive treatment three times weekly for 8 weeks. The primary outcome will be shoulder function and the secondary outcomes will include pain intensity, shoulder ROM, interleukin-6 (IL-6), depression, anxiety, and quality of life (QoL). All outcomes will be assessed at baseline, at post 8-week intervention, and at 3 months follow-up.

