### Primary outcome measure

The primary outcome measure is the shoulder function to be assessed using the Shoulder Pain and Disability Index (SPADI). It consists of 13 items divided into two subscales (5 items for shoulder pain and 8 items for shoulder disability). Each item is scored on a 0–10 numerical rating scale, where 0 denotes the best score and 10 denotes the worst score [49]. The scores of each subscale are added up and converted into a score out of 100, with higher scores indicating greater pain and disability [50]. The SPADI is a valid, reliable, and responsive measure of shoulder pain and disability [50–52]. Both the English [53] and Hausa (unpublished data) versions will be used in this study.

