### Sample size estimation

To our knowledge, no trial could be found evaluating the comparative effects of LLLT and MET among diabetic patients with frozen shoulder. However, given that the minimal clinically important difference (MCID) of the SPADI has been reported to be 8.0% points [67], the required sample size was estimated to detect a minimum difference of 8.0% (standard deviation [SD] = 10.0%) points in SPADI between the experimental groups (LLLT and MET) and control group (CTE) means post-intervention. Using the following parameters: F-test, repeated measures, between-subjects analysis of variance (ANOVA); alpha (*α*) level of 0.05; power of 0.80; effect size of 0.38 when accounting for 3 repeated measures; and correlation among repeated measures of 0.5, a total of 48 participants (16 participants per group) will be required for the trial. While anticipating an attrition rate of 25% (*n* = 12), the final sample size is 60, with 20 participants per group. Calculations were carried out using G Power 3.1.9.2 software [68].

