### Plans for assessment and collection of outcomes

All outcome measures will be collected at inclusion (baseline), at post 8-week intervention, and 3 months follow-up (Table 1).

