### Statistical methods for primary and secondary outcomes

The intention-to-treat principle will be the main analysis and will be conducted by including each participant's available data according to original allocation and irrespective of the level of attendance. A mixed between–within subjects ANOVA will be used to evaluate time effect (baseline, 8 weeks, 3 months), group effect (LLLT group, MET group, control group), and group-by-time interaction effect for all outcome measures. Post hoc analysis using Bonferonni correction will be applied for pairwise comparisons for significant differences detected in the primary outcome measures. Fisher's least significant difference (equivalent to no adjustment) will be applied to the secondary outcome measures. Effect size will be computed to describe the magnitude of change in all the outcomes. Potential confounding variables such as age, gender, BMI, and duration of DM will be controlled in the main analyses.

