## Discussion

Frozen shoulder is a common and burdensome musculoskeletal complication among diabetic patients but it seems to be generally less prioritised and poorly treated [11]. This oversight may be due to challenges in managing diabetes-related complications, prioritising glycemic control, and healthcare providers' limited awareness of musculoskeletal issues in diabetic patients.

Despite the availability of various physiotherapy interventions for frozen shoulder, there remains a notable lack of substantial evidence supporting the superiority of one intervention over another [29]. While both LLLT and MET are commonly employed in the management of frozen shoulder, the comparative effectiveness of these interventions remains unexplored. Additionally, there is a notable gap in the literature regarding the evaluation of the effectiveness of either intervention on inflammatory biomarkers and psychological variables. As such, a comprehensive investigation into the relative efficacy of LLLT and MET for frozen shoulder treatment, encompassing their effects on both clinical outcomes and potential underlying mechanisms, is warranted. This would not only provide insight into the most  optimal treatment approach for improving function in frozen shoulder but also illuminate the impact of these interventions on inflammatory cytokines  and psychological outcomes.

We hypothesize that patients undergoing 8-week LLLT or MET interventions will exhibit superior improvements in all outcomes compared to those undergoing 8-week CTE post-intervention and at 3 months follow-up. By elucidating the most optimal treatment approach for frozen shoulder in diabetic patients, our study could guide clinical practice.

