### Trial status

The study opened to participant recruitment on 2 February 2023. It is anticipated that recruitment will end by May 2024 and data collection (final follow-up) will be completed in August 2024.

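### No visit and no test is named as deciding the primary outcome (SPADI), and the sample size describes one target but is computed for another

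*Protocol article*

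**What the plan says.** The abstract (Methods) states "The primary outcome will be shoulder function". The section Primary outcome measure says "The primary outcome measure is the shoulder function to be assessed using the Shoulder Pain and Disability Index (SPADI", again with no visit. Under Plans for assessment and collection of outcomes, "All outcome measures will be collected at inclusion (baseline), at post 8-week intervention, and 3 months follow-up".

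Sample size estimation takes as its target a SPADI difference of 8.0 points with SD 10.0, and places that difference "between the experimental groups (LLLT and MET) and control group (CTE) means post-intervention". It then computes N with a repeated-measures, between-subjects F test using three measures, correlation 0.5 and effect size 0.38, which gives 48 (16 per group), raised to 60 for attrition.

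Statistical methods for primary and secondary outcomes fits a mixed ANOVA with time, group and group-by-time effects for every outcome. On multiplicity for the primary outcome it says "Post hoc analysis using Bonferonni correction will be applied for pairwise comparisons" where significant differences are found. Visits are not mentioned.

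The responder analysis is planned at both later visits without ranking them. The Hypotheses section names no visit. The Discussion expects "superior improvements in all outcomes compared to those undergoing 8-week CTE post-intervention and at 3 months follow-up".

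**The concern.** A primary outcome decides a trial only when the visit and the test are fixed along with the instrument. Here at least three answers could be presented as primary: the group effect over three visits, the group-by-time interaction, and pairwise contrasts at 8 weeks or at 3 months. They estimate different things and need not agree.

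The group effect averages in a baseline visit at which randomised arms are expected to be equal, so it dilutes any treatment effect. The interaction captures divergence over time but does not say at which visit. The pairwise contrasts give a clinical answer, but the plan does not say at which visit they are read, or whether they compare group means averaged over visits.

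If these disagree, the plan has no rule for which is the trial's result, and the choice could be made after the data are seen.

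**Working it through.** **Inputs.** From Sample size estimation: difference 8, SD 10, three measures, correlation 0.5, alpha 0.05, effect size f = 0.38, power 0.80, 16 per group before attrition and 20 after. Assumptions made here: arms equal at baseline, the same 8-point benefit for LLLT and MET over CTE at both later visits, normal data with equal correlation, no covariates.

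**1. The plan's own figure.** Group means 0, 8, 8 have mean 16/3 and standard deviation √(42.67/3) = 3.77. Divided by 10 this is f = 0.377, rounded to 0.38. For the between-subjects effect, λ = f² × N × m / (1 + (m − 1)ρ) = 0.1444 × 48 × 3 / 2 = 10.40 on 2 and 45 degrees of freedom. Power is 0.804, so N = 48 is reproduced. It belongs to a group effect averaged over three visits, and it holds only if the full 8-point difference is present at all three, including baseline.

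**2. The group effect if the benefit starts after baseline.** The averaged difference is 8 × 2/3 = 5.33 points, so f = 0.38 × 2/3 = 0.253. Then λ = 0.0642 × 144 / 2 = 4.62 and power is about 44%.

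**3. The interaction in the same scenario.** Squared group deviations sum to 42.67 and squared visit deviations (−2/3, 1/3, 1/3) sum to 0.667. With 16 per arm and within-subject error variance 100 × (1 − 0.5) = 50, λ = 16 × 42.67 × 0.667 / 50 = 9.10 on 4 and 90 degrees of freedom. Simulated power is about 64%.

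**4. Agreement of the two F tests (simulation, 16 per arm).**
- With the benefit above, one is significant and the other not in about half of trials.
- With no effect, at least one is significant in about 10% (0.098).

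**5. Pairwise claims under no effect in any arm**, three group pairs at 0.05/3 each:
- one visit: about 4% (0.043)
- either visit, with no preceding F test: about 8% (0.080; upper bound 6 × 0.05/3 = 0.10)
- either visit, only after a significant group or interaction F: about 4% (0.043)

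**6. Power of a single-visit pairwise contrast**, d = 8/10 = 0.8, alpha 0.05/3, pooled SD, noncentrality d × √(n/2):
- 16 per arm: 0.8 × √8 = 2.26, power 42%
- 20 per arm: 0.8 × √10 = 2.53, power 53%
- 80% power needs 34 per arm

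If baseline SPADI correlates 0.5 with the 8-week score, adjustment reduces the variance by the factor 1 − 0.25 = 0.75, so d becomes 0.8/√0.75 = 0.924. With one degree of freedom fewer, power is about 55% at 16 per arm and 67% at 20, and 26 per arm are needed for 80%.

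**The case against.** Several counter-arguments have force.

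- **The sized effect is tested.** N was computed for a group effect, and the analysis section does test one. A reader might infer from the post-intervention wording that the effect behind the sample size is never tested. That is not so. The conflict is inside the sample size section, between its wording and its computation.
- **Alpha.** A reader might infer that Bonferroni over group pairs leaves the two visits uncontrolled and inflates the error rate. The text says only pairwise comparisons, and applies them where significant differences are detected, which reads naturally as a gate. So gated, false pairwise claims stay at about 4% when no arm has an effect.
- **Conflicting verdicts between visits.** With a true benefit at both visits, the LLLT versus CTE verdict differs between 8 weeks and 3 months in about 33% of simulated trials. That mostly reflects low pairwise power. Naming a visit would not reduce it; it would only settle which result counts.
- **The follow-up date.** The article anticipates that "recruitment will end by May 2024 and data collection (final follow-up) will be completed in August 2024". Eight weeks plus three months from May runs to about October, whereas August fits three months from enrolment. The analysis section's list of baseline, 8 weeks and 3 months allows that reading, and the dates are only anticipated. This asks for a clarification and does not show a contradiction about the primary outcome.
- **An unseen analysis plan** might rank the tests. The article mentions one, but refers to it only for the per-protocol set. It states its own sizing target, model, post hoc rule and expectations, and these do not identify one deciding test.

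Hypothesising benefit at both visits is also compatible with a model using all visits. What stands after all this is the absence of a named visit and test, and the mismatch within the sample size section.

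**Conclusion.** The point holds in this limited form. Nothing in the article fixes which visit or which test decides SPADI, and the sizing text points to a post-intervention difference while its N comes from a three-visit average. This matters in practice: under the plan's own difference, SD and correlation, with the benefit appearing after baseline and 16 per arm, the two candidate F tests have about 44% and 64% power and disagree about half the time. Treating either as sufficient gives about a 10% chance of a significant F test under no effect.

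The documents do not support a charge of serious alpha inflation in the pairwise claims. The harm is that the primary answer is undefined. The figures rest on equal arms at baseline, a constant 8-point benefit in both experimental arms, equal correlations and no covariate adjustment; other patterns over time would change them.

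**What to change.** Before unblinding:

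- Name SPADI at the end of the 8-week intervention as the single primary endpoint, in line with the wording of the sample size section.
- Make the between-arm contrasts at that visit the deciding tests, adjusted for baseline SPADI (already collected), with Bonferroni over the group pairs.
- Make the 3-month visit and the other model effects secondary, and state whether 3 months is counted from enrolment or from the end of treatment.
- Restate the power in Sample size estimation for that test: about 42% at 16 per arm and 53% at 20 without baseline adjustment, and somewhat higher with it, as worked above.
- Align the abstract, Objectives, Primary outcome measure, statistical methods, Discussion and Trial status sections.

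No new data are needed, but this is more than rewording. A difference seen only at 3 months could no longer carry the primary claim, and the stated power becomes less favourable than 80%. The change also needs an amendment by the route the article describes, with ethics committee approval and a registry update.

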**Supplementary Information:**

The online version contains supplementary material available at 10.1186/s13018-024-04735-7.

## Background

Diabetes mellitus (DM) is one of the fastest-growing public health issues of the twenty-first century owing to its increasing prevalence rates, related morbidity and mortality, as well as health expenditures at global, regional and national levels [1, 2]. Approximately 537 million people are living with DM globally, and this number is projected to 643 million by 2030, and 783 million by 2045 [2]. Low-income countries, especially those in Sub-Saharan Africa are likely to bear one of the greatest burdens of DM epidemic as the number of individuals living with type 2 DM is expected to increase at the fastest rate in the coming decades. In 2021, South Africa was ranked the highest country for the number of people with DM (4.2 million) followed by Nigeria (3.6 million) [1]. The proportion of undiagnosed DM cases in Africa (67%) is almost twofold higher than that of developed countries (37%) [3], which may be linked to the high levels of morbidity and mortality at an early age in this continent [4].

Individuals with DM, especially those with poor glycemic control are at increased risk of debilitating and life-threatening complications resulting in increased disability, poor quality of life (QoL), reduced life expectancy, and considerable healthcare costs. Although microvascular and macrovascular complications are well-known and treated [5], musculoskeletal complications are also prevalent in DM [6–8]. Diabetics are 1.7–2.1 times more likely to experience musculoskeletal pain compared with non-diabetics [9], with a prevalence of 58.2% for musculoskeletal disorders (MSKD) [10]. Despite their impact on morbidity and pain [6], MSKD are generally overlooked compared to vascular complications, possibly because they are not life-threatening [11]. These complications stem from similar pathogenic factors as internal organ complications, including chronic low-grade inflammation [12].

A variety of MSKD have been well-documented to be associated with both type 1 and type 2 DM [7, 10]. The most commonly documented MSKD include carpel tunnel syndrome, Dupuytren's contracture, flexor tenosynovitis, frozen shoulder, limited joint mobility, and osteoarthritis [13, 14]. However, among the different disorders, fibrosing conditions affecting the hand were generally reported to be more prevalent (33.1%) followed by those affecting the shoulder (32%) [10].

Frozen shoulder is one of the common painful and disabling fibro-proliferative disorders characterized by a gradual onset of pain and limitation of glenohumeral range of motion (ROM) that can restrict activities of daily living without any radiological evidence [15, 16]. The odds of developing frozen shoulder for patients with DM was 3.7 times the odds for those without DM [17] and the overall prevalence of frozen shoulder among diabetics was estimated at around 13.4% (95% CI 10.2–17.2%) [18]. The impact of living with diabetic frozen shoulder is multifactorial including clinical factors such as severe pain, impaired mobility, and disability [19, 20] and psychosocial factors such as anxiety, depression, sleep deprivation, and altered domains of QoL [19, 21, 22]. Indeed, people with DM may experience worse outcomes from frozen shoulder than those without DM [23]. Frozen shoulder in diabetic patients is associated with the duration of DM and age [24], with those aged 40–59 years [25] and females [26] being more commonly affected.

The etiology of frozen shoulder in diabetes is not fully understood, but proposed mechanisms include impaired microcirculation and non-enzymatic glycosylation processes in the shoulder joint tissues [27]. Altered levels of inflammatory cytokines, such as interleukins, have also been linked to inflammation and fibrosis characteristic of frozen shoulder [28]. The management of frozen shoulder includes various approaches such as education, physiotherapy, medications, and surgery to alleviate pain and enhance ROM and function [29]. However, there is no consensus on the most effective single treatment approach, leading to a preference for combination therapies [30, 31].

Conventional therapeutic exercises (CTE) are typically prescribed alongside other interventions such as electrotherapy and mobilisation techniques to alleviate symptoms of frozen shoulder. Exercises regarded as CTE include Codman's or pendulum exercises, active and passive ROM, wall ladder exercises, capsular stretching, pulley, self-stretching, strengthening exercises, and shoulder mobilisation exercises [32, 33]. These exercises stimulate mechanoreceptors and improve joint lubrication and ROM thereby reducing inflammation and pain as well as enhancing function.

Among the several electrotherapy modalities employed in physiotherapy, low-level laser therapy (LLLT) emerges as a promising modality for the treatment of frozen shoulder owing to its analgesic, anti‐inflammatory and biostimulating effects [34]. A class IIIa LLLT with a power output of < 5mW or a class IIIb LLLT with a power output of < 500 mW is often applied to achieve optimal therapeutic effect [35]. However, LLLT is typically used in combination with other therapies such as exercise rather than in isolation. While moderate evidence indicates that LLLT offers added short-term pain relief benefits when combined with exercise, evidence for additional benefits on shoulder function and ROM is limited [36].

One hands-on technique commonly used by physiotherapists to manage MSKD such as frozen shoulder is the muscle energy technique (MET) [37, 38]. It is a class of gentle soft tissue manipulation applied to lengthen shortened, contracted, or spastic muscles, strengthen weak muscles, decrease edema and passive congestion, correct faulty joint positions, as well as mobilise restricted or hypomobile joints [39, 40]. As frozen shoulder often involves inflammation, reduced ROM and pain, the use of MET to address  these symptoms is crucial [41]. While MET has shown effectiveness in improving pain, disability, and ROM in various MSKDs, its efficacy in frozen shoulder specifically requires further evaluation [42]. Morever, existing trials on MET for frozen shoulder [43–46] have yielded conflicting results and lack methodological robustness.

Frozen shoulder constitutes a major burden in patients with diabetes, yet the most optimal treatment remains obscure. Although both LLLT and MET are used to manage frozen shoulder, the superiority of one intervention over the other has not been explored. Moreover, no study has evaluated the effect of either intervention on inflammatory biomarkers or psychological variables. Given that both LLLT and MET could alleviate pain and enhance function, which may result in improved psychological well-being, it is probable that such interventions could positively influence depression, anxiety as well as QoL. As there has been no investigation into the effectiveness of LLLT and MET and their comparison through a well-conducted randomised controlled trial (RCT) among diabetic patients with frozen shoulder, this study will be conducted to assess the comparative effectiveness of LLLT versus MET among diabetic patients with frozen shoulder.

## Objectives

The primary objective is to evaluate the effectiveness of an 8-week LLLT *versus* MET compared to CTE (control) on shoulder function among diabetic patients with frozen shoulder. The secondary objective is to evaluate the effectiveness of an 8-week LLLT *versus* MET compared to CTE on pain intensity, shoulder ROM, interleukin 6 (IL-6), depression, anxiety, and QoL.

### Hypotheses

We hypothesize that patients receiving either LLLT or MET would demonstrate superior improvement in terms of shoulder function, pain intensity, shoulder ROM, interleukin 6 (IL-6), depression, anxiety, and QoL compared to those receiving CTE.

## Materials and methods

### Trial design

This study is a single-centre, prospective, single-blind, RCT with three parallel groups: LLLT, MET, and CTE (control) in a 1:1:1 ratio. This protocol was written in accordance with the Standard Protocol Items: Recommendations for Interventional Trials (SPIRIT) guidelines (Additional file 1). The flow of participants through the study is depicted in Fig. 1.

